## Objectives {7}

The primary objective of this trial is to show that failure-free survival (FFS) after vsAR is non-inferior to tAR after 24 months of follow-up.

❖ Failure is defined as the inability to pass a 16-Fr flexible cystoscope through the reconstructed area without damaging the urethral mucosa.

❖ The non-inferiority limit, *d*, was set at 10%. This non-inferiority limit was chosen based on experts’ opinion, 5 patients’ opinion, and a round-the-table consensus discussion.

❖ The fact that failure after AR usually occurs within the first years after surgery serves as the rationale behind the follow-up interval of 24 months in this study [13].

Main research question, study hypothesis (Ha), and null hypothesis (H0) based on primary objective:
Is the FFS after vsAR not inferior to the FFS after tAR in isolated short bulbar urethral strictures?Study hypothesis (Ha): The FFS after vsAR is not inferior to the FFS after tAR in isolated short bulbar urethral strictures.Null hypothesis (H0): The FFS after vsAR is inferior to the FFS after tAR in isolated short bulbar urethral strictures.

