#### Analysis of the primary end-point

Kaplan-Meier curves for FFS will be plotted with the corresponding log-log 80% CIs for vsAR and tAR.

Non-inferiority of vsAR versus tAR in terms of FFS at 24 months will be concluded when the lower limit of the 80% CI for the difference in FFS probability at 24 months does not exceed − 10%. Note that this analysis does not take into account the nesting of patients within centers, which may affect the estimated standard errors.

To take into account the clustering of patients within centers, a marginal Cox proportional hazards model can be fitted (using the cluster function from the “survival” package in R software) which will give a robust estimation of the variance. The lower limit of the 80% CI for the hazard ratio can be transformed into a limit of survival difference at 24 months, assuming an exponential distribution of failure-free survival times [*S*(*t*) = exp.{−*λt*}].

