### Methods for additional analyses (e.g., subgroup analyses) {20b}

Interaction tests for FFS were considered for traumatic versus non-traumatic stricture etiology and for primary versus secondary procedures. However, the rule of thumb says that at least 10 failures are needed per degree of freedom included in the model. Allowing for a modification of the effect of procedure by stricture etiology for instance would imply adding 3 degrees of freedom to the model (technique, center, and stricture etiology). This would lead to overfitting, which means the obtained results might not be reproducible in other samples. We will refrain from generalizing our findings from these (over)complex models to the larger population of patients and stick to purely descriptive results when considering more than one explanatory covariate.

The PP analysis of de novo postoperative worsening of erectile function after vsAR and tAR will be performed as well (two-sided Fisher’s exact test at the 20% significance level) to explore the effect of full-thickness transection on postoperative erectile function.

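### The optional centre-clustered Cox analysis converts the lower limit of a hazard ratio whose direction is not defined; under the usual vsAR/tAR coding that limit is the best case for vsAR.

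*Protocol article*

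**What the plan says.** Protocol article, Analysis of the primary end-point, has two layers.

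- **The deciding rule.** What is to be judged is put as "Non-inferiority of vsAR versus tAR in terms of FFS at 24 months". The criterion holds the lower end of the two-sided 80% interval for the FFS difference against −10%. The section adds that this analysis ignores the nesting of patients within centres and that the standard errors may be affected.
- **The centre-clustered version.** "To take into account the clustering of patients within centers, a marginal Cox proportional hazards model can be fitted", with a robust variance. Then: "The lower limit of the 80% CI for the hazard ratio can be transformed into a limit of survival difference at 24 months". The model behind that conversion is given as "assuming an exponential distribution of failure-free survival times".

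The event is set in Objectives {7}: "Failure is defined as the inability to pass a 16-Fr flexible cystoscope through the reconstructed area without damaging the urethral mucosa". It is a harmful event, so a higher hazard is worse. The article does not say whether the hazard ratio is vsAR over tAR or the reverse, and it gives the Cox result no pass or fail criterion of its own.

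**The concern.** On the scale of the FFS difference (vsAR minus tAR), the lower limit is the unfavourable end for vsAR and is the right one to hold against −10%. On a hazard-ratio scale for failure coded vsAR/tAR, the direction flips: a low ratio is good for vsAR and a high ratio is bad. Carrying the words for the lower limit from one scale to the other selects the wrong end.

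The converted limit is on the same scale as the margin, so readers will set it beside −10%. This is also the only analysis offered for the centre effect that the main analysis admits to ignoring. If the wrong end is converted, the supportive result would look reassuring almost regardless of the data in the range that matters, including where the main interval fails.

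**Working it through.** **Inputs.** From Sample size {14}: FFS at 24 months 95.4% (tAR) and 95.3% (vsAR); one-sided alpha 0.10, so z = 1.2816; power 0.80; 41 per arm before drop-out, 50 per arm planned. From Objectives {7}: margin 10 percentage points. A 20% drop-out from 50 leaves 40 per arm.

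**Reproducing the plan's figure.** n = (1.2816 + 0.8416)² × (0.954×0.046 + 0.953×0.047) / (0.10 − 0.001)² = 4.508 × 0.088675 / 0.009801 = 40.8, so 41 per arm, as stated.

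**Step 1, direction.** With S(t) = exp(−λt) and HR = λ_vsAR/λ_tAR, S_vsAR = S_tAR^HR. This falls as HR rises, so the lower HR limit gives the upper limit of the FFS difference, and the upper HR limit gives the lower one.

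**Step 2, margin on the HR scale.** HR = ln(0.854)/ln(0.954) = 3.35. Coded vsAR/tAR, non-inferiority needs the upper 80% limit below 3.35. Coded tAR/vsAR, it needs the lower limit above 1/3.35 = 0.298.

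**Step 3, assumed example: 2/50 failures on tAR, 10/50 on vsAR.**
- HR = ln(0.80)/ln(0.96) = 5.47. SE of log HR = √(1/2 + 1/10) = 0.775. exp(1.2816 × 0.775) = 2.70. The 80% CI is 2.03 to 14.75.
- Lower limit: 0.96^2.03 − 0.96 = −3.9 points, which would pass.
- Upper limit: 0.96^14.75 − 0.96 = −41.2 points, which fails.
- Direct difference: −16.0 − 1.2816 × √(0.96×0.04/50 + 0.80×0.20/50) = −16.0 − 1.2816 × 6.30 = −24.1 points, which fails.
- Coded tAR/vsAR, the lower limit is 1/14.75 = 0.068, below 0.298, so it correctly fails.

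**Step 4, how often each check passes.** All pairs of failure counts were enumerated with binomial weights: 50 per arm, tAR FFS 95.4%, no drop-out, no centre effect. The HR was taken as ln(S_vsAR)/ln(S_tAR) with SE √(1/d1 + 1/d0) in place of a robust Cox fit, and the observed tAR survival was plugged in. HR columns count only trials with at least one failure in each arm.

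| True vsAR FFS | HR estimable | Lower HR limit passes | Upper HR limit passes | Direct difference passes (all trials) |
|---|---|---|---|---|
| 95.3% | 82.4% | 100% | 52.9% | 83.4% |
| 85.4% (margin) | 90.5% | 99.97% | 3.3% | 10.8% |
| 80% | 90.5% | 98.9% | 0.5% | 1.9% |
| 65% | 90.5% | 46% | 0.0% | 0.0% |

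Counted over all trials, the lower-limit check passes 0.989 × 0.905 = 90% at a true FFS of 80%, and 42% at 65%.

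**Step 5, sparse failures at the planned FFS.**
- Expected failures: 50×0.046 + 50×0.047 = 4.65, or 3.72 with 40 per arm.
- HR undefined because an arm has no failure: 1 − (1 − 0.954^50)(1 − 0.953^50) = 1 − 0.905 × 0.910 = about 18%. With 40 per arm: 1 − 0.848 × 0.854 = about 28%.
- Upper-limit check over all trials: 0.529 × 0.824 = about 44%, against 83% for the direct difference. With 40 per arm, the same enumeration gives about 26% against 82%.

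**The case against.** The strongest reply is that no rule in the protocol acts on this sentence. Non-inferiority is concluded from the FFS difference alone, with the correct limit. The Cox model is optional, is there to address the standard errors, and has no criterion attached; the check on the lower HR limit is a rule that a reader would have to supply. This stands. A reader might infer that the trial as planned would declare a clearly inferior technique non-inferior. The document does not support that: under the stated rule, about 1.9% of trials pass at a true vsAR FFS of 80%.

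The second reply is that the ratio's direction is never stated, and with tAR/vsAR the sentence is right. This also stands, and it makes the point conditional. It does not remove it: experimental over control is the usual coding, it matches the section's only stated direction, and a named limit has no fixed meaning until the direction is given.

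Nor is it right to say that the lower-limit check could never detect inferiority. It fails once the lower limit passes about 3.35, and at a true FFS of 65% it fails more than half of the estimable trials. It is a very weak check, but it does respond to the data.

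Three neighbouring criticisms are not pressed. How the uncertainty of the tAR survival enters the conversion is detail that an article may leave to the analysis plan. The rule of thumb that "at least 10 failures are needed per degree of freedom included in the model" is used in {20b} to decline models with several covariates, and turning it against a one-parameter randomised comparison stretches it. Replacing the Cox step by a centre-stratified difference is a matter of choice, since with so few failures many strata would probably have none.

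**Conclusion.** The point holds as a defect in the supportive analysis. The direction of the hazard ratio is undefined, and under the usual coding the limit named is the wrong one. Under that coding, a check on it would pass nearly every estimable trial at the margin, where the design allows 10%, and about 99% at a true vsAR FFS of 80%. The primary conclusion is untouched.

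The figures assume exponential failure times, an approximate log-HR standard error, plug-in tAR survival, no drop-out and no centre effect. The direction of the error follows from S_vsAR = S_tAR^HR and needs none of the approximations in the pass rates.

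A smaller wording matter sits in the deciding rule itself. Non-inferiority is concluded "when the lower limit of the 80% CI for the difference in FFS probability at 24 months does not exceed" −10%, which taken literally is a limit at or below −10%, the reverse of what is meant. The objective and hypotheses leave only one sensible reading, so this is an editorial correction.

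**What to change.** In Analysis of the primary end-point:

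1. Define the hazard ratio as vsAR/tAR and convert its upper 80% limit. Alternatively, define it as tAR/vsAR and keep the lower limit.
2. State that the FFS difference decides and that the Cox result is supportive.
3. Reword the deciding rule: non-inferiority is concluded if the lower limit of the two-sided 80% CI for FFS(vsAR) minus FFS(tAR) is greater than −10 percentage points.

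The edit is a few words, needs no new data, and should be made before analysis. It has a price: the correct limit is far less favourable to vsAR than the one named. At the planned FFS it would often miss the margin when the direct difference meets it, and in a sizeable share of trials there would be no hazard ratio to convert. That is why the supportive status in item 2 should be fixed in advance, together with a sentence on what is reported when an arm has no failures.

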#### Analysis of the secondary end-points

Postoperative changes in erectile function, ejaculatory function, LUTS, urinary incontinence, and quality of life will be analyzed by comparing the scores of the postoperative questionnaires with the scores of the preoperative questionnaires. For every participant, the 3-, 12-, and 24-month follow-up questionnaire scores will be compared to the respective preoperative questionnaire scores. Differences in scores will be logged for the 3-, 12-, and 24-month follow-up moment, and for each of these time-points, the median (interquartile range (IQR)) change in scores will be assessed for vsAR and tAR. Median (IQR) change in scores will be compared between vsAR and tAR using a two-sided Mann-Whitney *U* test at the 20% significance level.

As regards de novo postoperative worsening of erectile function, defined as a decrease of ≥ 5 points on the postoperative IIEF-5 questionnaire compared to the preoperative IIEF-5 questionnaire, a two-sided Fisher’s exact test at the 20% significance level will be used to compare vsAR and tAR at the 3-, 12-, and 24-month follow-up moment.

Postoperative patient satisfaction will be assessed at the 3-, 12-, and 24-month follow-up moment. For each time-point, the proportion of satisfied patients will be compared between vsAR and tAR using a two-sided Fisher’s exact test at the 20% significance level.

Postoperative change in Qmax will be compared between vsAR and tAR at the 3-, 12-, and 24-month follow-up moment using a two-sided Mann-Whitney *U* test at the 20% significance level.

Postoperative complications will be compared between vsAR and tAR using a two-sided Fisher-Freeman-Halton test at the 20% significance level.

Note that for all secondary end-points, participants will be censored at the moment they undergo a subsequent urethral treatment (dilation, urethrotomy, urethroplasty, or urinary diversion).

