To analyze change in erectile function and differences in change of erectile function between vsAR and tAR.❖ The International Index of Erectile Function (IIEF-5) questionnaire* will be administered to participants preoperatively and after 3, 12, and 24 months of follow-up.❖ The IIEF-5 questionnaire provides a summative score between 5 and 25 and should be interpreted as follows: 22–25 = no erectile dysfunction; 17–21 = mild erectile dysfunction; 12–16 = mild to moderate erectile dysfunction; 8–11 = moderate erectile dysfunction; 5–7 = severe erectile dysfunction.❖ De novo postoperative worsening of erectile function will be defined as a decrease of ≥ 5 points on the postoperative IIEF-5 questionnaire compared to the preoperative IIEF-5 questionnaire. This definition was chosen based on experts’ opinion, taking into account the lack of studies describing the ideal cut-off value to delineate “de novo erectile dysfunction” for this 5-item questionnaire [12].To analyze change in ejaculatory function and differences in change of ejaculatory function between vsAR and tAR.❖ The Male Sexual Health Questionnaire—Ejaculatory Dysfunction short form (MSHQ-EjD short form) questionnaire** will be administered to participants preoperatively and after 3, 12, and 24 months of follow-up.❖ The MSHQ-EjD short form questionnaire, consisting of 4 questions, provides a summative score between 1 and 15 (question 1–3) and a bother/satisfaction score between 0 and 5 (question 4).To analyze change in lower urinary tract symptoms (LUTS) and differences in change of LUTS between vsAR and tAR.❖ The International Consultation on Incontinence Questionnaire—Male Lower Urinary Tract Symptoms module (ICIQ-MLUTS module) questionnaire** will be administered to participants preoperatively and after 3, 12, and 24 months of follow-up.❖ The ICIQ-MLUTS module, consisting of 7 questions, provides a summative score between 0 (asymptomatic) and 24 (most symptomatic) (question 1–6) and a bother score between 0 (not bothersome) and 3 (very bothersome) (question 7).❖ Remark: The 7 questions of the ICIQ-MLUTS module questionnaire are only a subset of the entire ICIQ-MLUTS questionnaire. These 7 questions were chosen because of their relevance in a setting of urethral stricture disease and were validated in English, Dutch, and other languages (cfr. infra).❖ Peeling’s voiding picture** will be administered to participants preoperatively and after 3, 12, and 24 months of follow-up.❖ Peeling’s voiding picture provides a score between 1 and 4.To analyze change in urinary incontinence and differences in change of urinary incontinence between vsAR and tAR.❖ The International Consultation on Incontinence Questionnaire—Urinary Incontinence short form (ICIQ-UI short form) questionnaire will be administered to participants preoperatively and after 3, 12, and 24 months of follow-up.❖ The ICIQ-UI short form questionnaire, consisting of 3 scoring questions and 1 self-diagnostic question, provides a summative score between 0 (asymptomatic) and 21 (most symptomatic).To analyze change in quality of life and differences in change of quality of life between vsAR and tAR.❖ The EQ-5D-3L questionnaire** will be administered to participants preoperatively and after 3, 12, and 24 months of follow-up.❖ The EQ-5D-3L module, consisting of 5 questions, provides a 5-digit score in which every digit varies between 1, 2, and 3.❖ The EQ—Visual Analogue Scale (EQ-VAS)** will be administered to participants preoperatively and after 3, 12, and 24 months of follow-up.❖ The EQ-VAS provides a scale between 0 and 100.To analyze patient satisfaction and differences in patients’ satisfaction between vsAR and tAR.❖ Two specific questions regarding patient satisfaction will be asked at 3, 12, and 24 months.To analyze change in maximum flow rate (Qmax) and differences in Qmax between vsAR and tAR.❖ Uroflowmetry will be performed preoperatively and after 3, 12 and 24 months of follow-up.To analyze postoperative (< 90 days) complication rate and differences in postoperative (< 90 days) complication rate between vsAR and tAR.❖ Complications within the first 90 postoperative days will be categorized according to the Clavien-Dindo classification system [15, 16].

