## Assignment of interventions: allocation

### Sequence generation {16a}

Random allocation of patients to one of both treatment arms will occur through a computer-based random sequence generator with permuted blocks of variable size. Randomization will be stratified by participating center.

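### Questionnaire scores and Qmax are compared as unadjusted change from baseline; adjusting for the preoperative value and centre could gain precision at no data cost, though the planned test is valid

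*Protocol article*

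**What the plan says.** The section on analysis of the secondary end-points fixes the method outcome by outcome, so it is not a detail left to an analysis plan. For each man "the 3-, 12-, and 24-month follow-up questionnaire scores will be compared to the respective preoperative questionnaire scores", and then "Median (IQR) change in scores will be compared between vsAR and tAR using a two-sided Mann-Whitney" U test, two-sided at the 20% level. Qmax follows the same pattern: "Postoperative change in Qmax will be compared between vsAR and tAR at the 3-, 12-, and 24-month follow-up moment using a two-sided Mann-Whitney" U test.

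The baseline data exist. Under Outcomes {12} each questionnaire "will be administered to participants preoperatively and after 3, 12, and 24 months of follow-up", and uroflowmetry is also done before surgery.

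On centre, Sequence generation {16a} says "Randomization will be stratified by participating center". For the primary end-point the protocol admits the omission ("Note that this analysis does not take into account the nesting of patients within centers") and offers a remedy: "To take into account the clustering of patients within centers, a marginal Cox proportional hazards model can be fitted". The secondary end-points have no counterpart.

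The section on additional analyses {20b} explains why interaction models for failure-free survival (FFS) were not pursued: "the rule of thumb says that at least 10 failures are needed per degree of freedom included in the model". It closes by limiting any analysis with more than one covariate to description.

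**The concern.** Subtracting the baseline fixes its coefficient at 1. If the true slope of follow-up on baseline differs from 1, the change score keeps noise that a model with baseline as a covariate would remove. Centre was used to balance the arms but is not used in these tests.

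Functional benefit is the stated reason for developing the vessel-sparing technique, and the Discussion expects the trial to settle whether that benefit is real. Yet the sample size rests on FFS alone, and no power or precision figure is given for the functional outcomes. With about 40 evaluable men per arm, avoidable noise matters. The closing sentence of {20b}, read literally, could also be taken to rule out an adjusted functional analysis, although its reasoning is about scarce failures.

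**Working it through.** **The plan's own figure.** The only stated calculation is for FFS: control 95.4%, experimental 95.3%, margin 10%, one-sided alpha 0.10, power 0.80.

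n = (1.2816 + 0.8416)² × (0.954×0.046 + 0.953×0.047) / (0.10 − 0.001)² = 4.508 × 0.08868 / 0.009801 = 40.8, so 41 per arm, as stated. The planned 50 matches 41 × 1.2 = 49.2 rounded up. After 20% drop-out, 50 × 0.8 = 40 men per arm remain for the scores. Censoring men at a further urethral treatment may lower this slightly.

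**Variance of the two estimators.** Let s_pre and s_post be the SDs and ρ the pre/post correlation. Each variance below is multiplied by 2/n for the between-arm contrast.

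- Change score: s_pre² + s_post² − 2ρ·s_pre·s_post
- Baseline-adjusted (ANCOVA): s_post²(1 − ρ²)
- Difference: (s_pre − ρ·s_post)², which is never negative and is zero only when ρ·s_post/s_pre = 1

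**Equal SDs (assumed).** The ratio of adjusted to change-score variance is (1 − ρ²)/[2(1 − ρ)] = (1 + ρ)/2. The last column takes an effect for which the change score has 80% power at two-sided alpha 0.20, with normal outcomes.

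| ρ (assumed) | Variance ratio | Adjusted n per arm matching 40 on change | Power of ANCOVA |
|---|---|---|---|
| 0.3 | 0.65 | 26 | 91% |
| 0.5 | 0.75 | 30 | 88% |
| 0.7 | 0.85 | 34 | 85% |
| 0.8 | 0.90 | 36 | 83% |

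**Unequal SDs.** Set s_pre = 1.

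- s_post = 1.5, ρ = 0.5: change 1 + 2.25 − 1.5 = 1.75; adjusted 2.25 × 0.75 = 1.6875; ratio 0.96.
- s_post = 1.5, ρ = 0.7: change 1 + 2.25 − 2.1 = 1.15; adjusted 2.25 × 0.51 = 1.1475; ratio 0.998.
- s_post = 0.75, ρ = 0.5: change 1 + 0.5625 − 0.75 = 0.8125; adjusted 0.5625 × 0.75 = 0.4219; ratio 0.52.

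So the gain can nearly vanish if spread widens after surgery, and can exceed the equal-SD figures if spread narrows.

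**The planned test itself.** The formulas above compare mean-based analyses, whereas the plan uses a rank test on bounded scores. A simulation therefore used a rounded score limited to 5–25, 40 men per arm, 5 centres with allocation balanced within centre, near-equal pre/post SDs, a 0.4 SD effect and two-sided alpha 0.20. All of these except the score range, the 40 per arm and the alpha are assumptions. There were 1,500 runs per setting for power and 1,000 for the null.

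| ρ | Centre share of variance | Mann-Whitney on change | Rank ANCOVA + centre |
|---|---|---|---|
| 0.3 | 0 | 55% | 69% |
| 0.5 | 0 | 69% | 76% |
| 0.7 | 0 | 82% | 84% |
| 0.3 | 0.1 | 56% | 71% |
| 0.5 | 0.1 | 68% | 78% |
| 0.7 | 0.1 | 80% | 86% |

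**Share due to centre.** Adding centre to ordinary ANCOVA moved power from 70.1% to 72.0%, 76.5% to 78.6% and 85.2% to 86.9% at a centre share of 0.1, that is, about 2 points. With no centre effect it added nothing.

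**Validity.** With no treatment effect the Mann-Whitney test on change rejected in 17% to 23% of runs, against a nominal 20%.

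**The case against.** The plan has a fair defence. The Mann-Whitney test is prespecified, distribution-free and suited to bounded, possibly skewed scores. It holds its level, and these are secondary end-points of a phase II trial sized for another outcome. All of that stands. It limits the weight of the point but gives no reason to leave baseline out, because the simulated gain persists in a rank-based analysis.

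Several stronger readings are tempting, and the documents do not support them:

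- A reader might infer that baseline is ignored. It is not: each man's preoperative value is subtracted. What is absent is adjustment for it.
- A reader might infer that chance baseline imbalance biases the result. Under randomisation such imbalance is part of the sampling error that the test already allows for. It costs precision.
- A reader might infer that a change score over-corrects whenever ρ is below 1, and is noisier than follow-up alone whenever ρ is below 0.5. Both statements need equal SDs. In general the first depends on the slope ρ·s_post/s_pre, and the second has its threshold at s_pre/(2·s_post). Equal SDs are doubtful for Qmax, where repair relieves obstruction.
- A reader might infer that leaving out centre is a serious fault. Its contribution here is about 0 to 2 power points, and the protocol's caveat on nesting concerns the FFS analysis only.

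**Conclusion.** The point holds as a matter of efficiency on secondary end-points. The planned comparison is valid, but asymptotically it can only equal or fall short of a baseline-adjusted one under a linear model, and the adjustment needs nothing that is not already collected.

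The size is uncertain because the protocol gives neither SDs nor correlations. With equal SDs the variance reduction is 35% at ρ = 0.3, falling to 10% at ρ = 0.8. In the simulation closest to the planned test, without a centre effect, the gain was about 13 power points at ρ = 0.3, 7 at 0.5 and 2 at 0.7. Unequal SDs can push the gain towards zero or make it larger. Nearly all of it comes from baseline.

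The failures-per-degree-of-freedom argument in {20b} is no defence: it concerns rare FFS events, not scores observed in about 80 to 100 men. This is a worthwhile improvement of modest weight and does not touch the primary conclusion.

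**What to change.** In the section on analysis of the secondary end-points:

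1. For IIEF-5, MSHQ-EjD, ICIQ-MLUTS, ICIQ-UI, EQ-VAS and Qmax, analyse the follow-up value at each visit in a model with treatment, preoperative value and centre. Use rank ANCOVA or proportional odds for bounded or skewed scores, and ANCOVA otherwise.
2. Report the adjusted treatment effect with its confidence interval.
3. Keep the Mann-Whitney test on change from baseline as a sensitivity analysis.

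In the section on additional analyses {20b}, state that the restriction to descriptive results with more than one covariate applies to FFS only.

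The cost is analysis wording. No new data, visits or patients are needed. The change should be fixed before the comparative functional data are analysed.

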### Sample size {14}

Power analysis and sample size calculation for this non-inferiority trial were performed using an online software package:

Sealed Envelope Ltd. 2012. Power calculator for binary outcome non-inferiority trial. [Online] Available from: https://www.sealedenvelope.com/power/binary-noninferior/ [Accessed Mon Apr 162,018].

Different scenarios were simulated, of which the results are discussed below. In all scenarios, 10% was considered the non-inferiority limit, *d*, as mentioned above.

- Scenario 1: power 0.80; estimated success in control group (tAR): 95.4%; estimated success in experimental group (vsAR): 95.3%; for different one-sided alphas:

❖ Alpha 0.025: 72 patients per arm

❖ Alpha 0.05: 56 patients per arm

❖ Alpha 0.10: 41 patients per arm

- Scenario 2: power 0.80; estimated success in control group (tAR): 95.4%; estimated success in experimental group (vsAR): 95.4%; for different one-sided alphas:

❖ Alpha 0.025: 69 patients per arm

❖ Alpha 0.05: 55 patients per arm

❖ Alpha 0.10: 40 patients per arm

- Scenario 3: power 0.80; estimated success in control group (tAR): 97.4%; estimated success in experimental group (vsAR): 93%; for different one-sided alphas:

❖ Alpha 0.025: 227 patients per arm

❖ Alpha 0.05: 179 patients per arm

❖ Alpha 0.10: 131 patients per arm

The numbers that were put in the above simulations are based on an in-home analysis of patients who underwent anastomotic repair at Ghent University Hospital between 2000 and 2017. Herein the FFS at 24 months for vsAR and tAR were 95.3% (standard deviation (SD), 2.3%) and 95.4% (SD, 2.0%) respectively. These exact results are represented in scenario 1. Scenario 2 represents a situation in which the surgical outcome would be exactly the same for vsAR and tAR. Scenario 3 represents a less favorable situation in which vsAR has a 24 m-FFS of 93% (95.3% − SD) and tAR has a 24 m-FFS of 97.4 (95.4% + SD).

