In every scenario, the power was set at 0.80, according to the guidelines for designing a phase II trial [21]. The results for different alphas are displayed above. Usually, a non-inferiority trial demands a significance level, alpha, of 0.025 as these trials only look at one boundary of the classic two-sided 95% confidence interval (CI) [22]. However, these conditions often lead to (sometimes unreasonably) high sample size calculations requiring excessive financing and recruitment. As a solution, researchers often design a phase II trial that allows for more coincidence and thus a trial with a higher significance level, alpha. Rubinstein et al. reported alpha values of 0.10 and 0.20 to be allowed in a phase II trial [21]. Considering the fact that a non-inferiority trial relies on one-sided testing, we believe a one-sided significance level, alpha, of 0.10 is allowed and most feasible.

Considering all of the above, a scenario in which the power is set at 0.80, the one-sided significance level, alpha, is set at 0.10, the estimated success in control group is set at 95.4%, and the estimated success in experimental group is set at 95.3% was found most realistic and feasible. Considering this and accounting for a realistic drop-out of 20% (experience based), it was estimated that each arm has to consist of 50 patients, resulting in a total sample size of 100 patients.

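### Fisher's exact test for erectile worsening and satisfaction is valid but runs below its 20% level; Boschloo's test would keep that level with equal or better power

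*Protocol article*

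**What the plan says.** In the protocol article, under Analysis of the secondary end-points, de novo erectile worsening is a binary outcome, "defined as a decrease of ≥ 5 points on the postoperative IIEF-5 questionnaire compared to the preoperative IIEF-5 questionnaire". The plan for testing this outcome is that "a two-sided Fisher’s exact test at the 20% significance level will be used to compare vsAR and tAR", separately for each of the three visits. For satisfaction at the same visits, "the proportion of satisfied patients will be compared between vsAR and tAR using a two-sided Fisher’s exact test at the 20% significance level". Both are intention-to-treat comparisons. Under Methods for additional analyses {20b}, the per-protocol comparison of erectile worsening again uses a "two-sided Fisher’s exact test at the 20% significance level".

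Under Sample size {14}, the chosen scenario reads "Alpha 0.10: 41 patients per arm". The article then allows for 20% of men being lost and concludes that "it was estimated that each arm has to consist of 50 patients, resulting in a total sample size of 100 patients". That calculation concerns failure-free survival only. The article gives no event rate, power or attained level for the two binary end-points.

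**The concern.** Fisher's test conditions on the total number of events. With 40 to 50 men per arm few tables are then possible, so the rejection probability under equal rates cannot get close to 20%. The sponsor argues for relaxed error levels so that a small trial stays feasible, and the conditional test takes part of that relaxation back. How much it takes back depends on the unknown event rate and on accidents of arm size.

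Protection of erectile function is one of the main benefits that the Introduction hopes for from sparing the vessels, and the Discussion expects the trial to confirm or refute such benefits. Power for the binary erectile outcome is modest under plausible rates, so a few points that cost nothing are worth having. The many comparisons at 20% raise a separate multiplicity question. Conservatism that varies with the event rate is not a way of answering it.

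**Working it through.** **Inputs from the article.** Two-sided Fisher test at 0.20; 1:1 allocation; 50 per arm; 20% drop-out; randomization in permuted blocks stratified by center. **Assumed, because the article gives none:** event rates.

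**1. The plan's own figure.** For scenario 1, n per arm = [p₁(1−p₁) + p₂(1−p₂)] × (z₀.₉₀ + z₀.₈₀)² / (d − (p₁ − p₂))².

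(0.954×0.046 + 0.953×0.047) × (1.2816 + 0.8416)² / (0.10 − 0.001)² = 0.088675 × 4.508 / 0.009801 = 40.8, so 41 as stated. With 50 per arm and 20% drop-out, 50 × 0.8 = 40 evaluable per arm. The relevant sizes are therefore about 40 to 50 per arm.

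**2. Method.** All pairs (x₁, x₂) of two independent binomials were enumerated. Fisher rejects if its two-sided p (the sum over tables no more probable than the observed one) is at most 0.20. Boschloo uses that same p as its ordering statistic. It rejects if p is at most c, where c is the largest cut-off whose rejection probability, maximised over the common event rate, stays at or below 0.20. Fisher itself never exceeds 0.20, so c is at least 0.20, and every table that Fisher rejects is also rejected by Boschloo. The cut-offs are c = 0.258 at 40/40 and 0.269 at 50/50.

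One table shows the effect. With 4/40 v 9/40 events, Fisher gives p = 0.225 (not significant at 20%) and Boschloo p = 0.153 (significant).

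**3. True level, common event rate 5–30%.**

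| Evaluable arms | Fisher | Boschloo, maximum over all rates |
|---|---|---|
| 40/40 | 4.5 to about 13% | 19.5% |
| 50/50 | 6.0–13.7% | 19.3% |
| 49/50 | 9.7–16.6% | 19.6% |
| 48/50 | 12.0–17.0% | 19.9% |
| 39/41 | 10.1–16.2% | 19.5% |
| 38/42 | 9.7–15.8% | 19.7% |
| 44/47 | 11.2–17.0% | 19.9% |

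**4. Power.** Equal arms: Fisher to Boschloo. Unequal arms: gain in points, with the range covering which arm is the smaller.

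| Assumed rates | 50/50 | 40/40 | 49/50 | 39/41 | 44/47 |
|---|---|---|---|---|---|
| 25% v 10% | 0.69 to 0.75 | 0.60 to 0.65 | 1.3–1.4 | 2.9–3.1 | 0.0 |
| 20% v 10% | 0.46 to 0.53 | 0.38 to 0.43 | 0.9–1.1 | 3.4–3.6 | 0.0–0.2 |
| 15% v 5% | 0.54 to 0.63 | 0.43 to 0.49 | 1.5–2.3 | 1.5–5.2 | 0.0–3.1 |
| 30% v 15% | 0.62 to 0.69 | 0.54 to 0.59 | 1.6–1.8 | 2.8–3.2 | 0.0 |
| 10% v 2% | 0.47 to 0.62 | 0.35 to 0.50 | 6.9 | 6.3–6.6 | 0.0–6.8 |

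The equal-arm gain also varies with n: at 41/41 it reaches 11.0 points for 15% v 5%.

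**5. Which case is likelier?** If 50 men per arm are each retained independently with probability 0.8, the chance of exactly equal evaluable arms is Σₖ [C(50,k) 0.8ᵏ 0.2⁵⁰⁻ᵏ]², about 0.10. Averaged over 150 random draws of the evaluable arms on that assumption, Fisher's level is about 9–15%. Boschloo's mean gain is then about 3.5 points (25% v 10%), 4.0 (20% v 10%), 4.5 (15% v 5%), 3.6 (30% v 15%) and 7.4 (10% v 2%).

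**The case against.** The strongest defence is that nothing in the plan is wrong. Fisher's test is standard and pre-specified, and it keeps its error at or below the nominal level. An attained level below 20% is a property of discrete data and contradicts no statement in the article. **This stands**, and it limits the point to efficiency.

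The second defence is that the larger figures depend on exactly equal arms, where Fisher is at its most conservative. Drop-out, center-stratified blocks and the post-hoc exclusion of men switched to another technique make equal arms unlikely. In the per-protocol analysis, converted men also move from vsAR to tAR. **This stands too.** A reader might infer from the equal-arm results that Fisher wastes about a tenth of the patients, since Boschloo with 45 per arm (0.71) beats Fisher with 50 (0.69) at 25% v 10%. The documents do not support that reading. Removing a single man (49/50) raises Fisher's own power in that scenario to 0.70–0.75, so the comparison mostly reflects discreteness at equal arms and cannot be converted into patients lost.

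Third, erectile change is also compared as an IIEF-5 score by the Mann-Whitney test, so the binary outcome does not carry the question alone. That is true and lowers the stakes. It is no reason to prefer the weaker of two valid tests for the binary outcome.

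**Conclusion.** The point holds as an avoidable loss of efficiency in secondary end-points. Boschloo's test, ordered by the two-sided Fisher p-value, keeps the 20% guarantee and had power equal to or above Fisher's at every arm size tried. The gain is about 5–8 points at equal arms of 40 or 50, and about 15 for rare events. It is usually 0–5 points at slightly unequal arms, and up to about 7 for rare events. The unequal-arm figures are the ones to expect in this trial.

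All power figures rest on assumed event rates, and the averages in step 5 also assume independent 20% drop-out in each arm. A reader might go further and call the Fisher test a mistake or a breach of the stated level. It is neither, because 20% is a ceiling and Fisher respects it. The primary non-inferiority analysis and the sample size are unaffected.

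**What to change.** Before outcome data are analysed, make two edits:

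- Under Analysis of the secondary end-points, replace Fisher's exact test by Boschloo's exact unconditional test, two-sided at the 20% level, for de novo erectile worsening and for satisfaction at 3, 12 and 24 months.
- Under Methods for additional analyses {20b}, make the same replacement for the per-protocol erectile analysis, so that both analyses of this end-point use one test.

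The text should state that the two-sided Fisher p-value is the ordering statistic, because the guarantee of never losing power to Fisher rests on it. The choice of unconditional test matters: Barnard's test with the pooled z statistic gains only 1–3 points over Fisher at several mid-range rates with 40 per arm.

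The cost is a change of wording. It needs no further patients or visits, and the 20% guarantee is kept.
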